### Statistical analysis

Prevalence of (previously unrecognised) heart failure (systolic and 'isolated' diastolic) will be calculated with exact 95% confidence intervals. The crude association of each diagnostic test (including the 'clinical score') with the presence or absence of HF will first be quantified by calculating predictive values, sensitivity, specificity and likelihood ratios by using univariate logistic regression analysis. Those with a p-value < 0.15 in the univariate analysis will subsequently be included in a multivariate logistic regression analyses to determine their independent contribution to the diagnosis of HF. In the analyses the chronology in which investigations are performed in practice will be followed. First of all, the diagnostic value of the signs and symptoms score will be assessed. Then NT-proBNP and ECG will be added, first separately and then in different combinations, to quantify their added diagnostic value, using the likelihood ratio test at a p-value of < 0.10 [32]. Areas under the ROC curve will be calculated for different combinations of the parameters to further quantify the diagnostic accuracy. Echocardiographic variables will not be evaluated separately on their diagnostic value because they would likely receive an overriding weight in the consensus judgement (i.e. diagnostic outcome assessment) [33]. In the cost-effective analysis, however, a separate diagnostic strategy to detect previously unrecognised HF by means of echocardiography only, will be evaluated, based on the echocardiographic findings. To assess the impact of heart failure, and diagnosis and treatment of heart failure in diabetes type 2 patients on health status, the scores on the Health status questionnaires of the three groups (no heart failure, known heart failure and previously unknown heart failure) will be compared at baseline (t0) and on 3 months and 12 months. Also the difference between 0-3 months, 3-12 months and 0-12 months within patients, will be compared between the groups (T-test and ANOVA).

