### Power calculation

When the diagnostic value of several diagnostic variables or tests together needs to be quantified, no straightforward methods to estimate the required sample size are available. A 'rule of thumb' for each diagnostic determinant included in the analysis is at least 10 events in the smallest category (in our study those with heart failure) is recommended. Our study will include at the most 9 diagnostic determinants (e.g. items from history and physical examination summarised in a score, ECG, and NT-proBNP). Thus, 90 patients with previously unknown heart failure would be required. With an estimated prevalence rate of 15% of previously unknown heart failure, about 600 diabetic type 2 patients should participate. Assuming, based on previous experiences, a response rate of at least 50%, approximately 1200 patients will be invited.

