### Cost-effectiveness analysis

A cost-effectiveness analysis of different strategies to detect unrecognized HF in patients with type 2 diabetes will be performed based on a social perspective according to international and national guidelines [31]. As a result of the primary data-analysis, various diagnostic strategies will be identified which differ in terms of the tests that are performed, the order of the tests, and the cut-off points used. Each strategy and each cut-off-point leads to different numbers of patients who are diagnosed as true positive (TP), false positive (FP), true negative (TN) and false negative (FN). To estimate the costs associated with these categories (FP, TP, FN, TN) a previously used and validated Markov model will be applied. The various strategies will be ranked by increasing cost-effectiveness ratios; the most optimal strategy in terms of cost effectiveness will be defined. It is important to note that there may be discrepancies in the most effective diagnostic strategy and the most cost-effective diagnostic strategy. The incremental cost-effectiveness of those tests that add to the best available diagnostic strategy, compared to the sub-optimal diagnostic strategy is of importance, in other words the additional value of the more expensive and most discriminating tests. For measuring direct costs, resource quantities are collected from the case record forms, and prices will be based on market prices or tariffs for the investigations performed in the study. Only relevant indirect medical costs are taken into consideration such as patient time and travel costs. When comparing diagnostic strategies, however, indirect costs are less relevant because all investigations can be performed in a single setting at the outpatient department, irrespective of the number of investigations. Both absolute costs and incremental costs of different diagnostic strategies will be taken in consideration.

A sensitivity-analysis will be performed in order to estimate the susceptibility of cost-effectiveness ratio's to variation in prior assumptions and choices, including a 'worst case - best case' comparison.

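### Tests, cut-offs and strategies are chosen in the same patients whose accuracy then ranks them, so apparent accuracy is optimistic (about 1 to 7.5 points of sensitivity under assumed conditions)

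*Protocol article*

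**What the plan says.** Statistical analysis section, protocol article:

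- Each test is first related to heart failure on its own. "Those with a p-value < 0.15 in the univariate analysis will subsequently be included in a multivariate logistic regression analyses".
- The signs-and-symptoms score comes first. NT-proBNP and ECG are then added, singly and in several combinations, with a likelihood ratio test at p < 0.10 for added value. AUCs are calculated for the combinations.
- Echocardiography is kept out of this modelling, but an echocardiography-only strategy is evaluated in the cost-effectiveness analysis.

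Cost-effectiveness analysis section: the primary analysis yields a set of strategies "which differ in terms of the tests that are performed, the order of the tests, and the cut-off points used". Each strategy and each cut-off gives its own true-positive, false-positive, true-negative and false-negative counts. A Markov model attaches costs to these categories, the strategies are ranked, and the best is named. A sensitivity analysis varies prior assumptions and choices, with a worst-case and best-case comparison.

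Power calculation section: "Our study will include at the most 9 diagnostic determinants", with "at least 10 events in the smallest category" for each. The case requirement follows: "Thus, 90 patients with previously unknown heart failure would be required". The number of participants is then set from the assumed prevalence: "With an estimated prevalence rate of 15% of previously unknown heart failure, about 600 diabetic type 2 patients should participate".

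**The concern.** Finding the most cost-effective strategy is a primary objective. As written, one data set chooses the determinants, the combinations, the order and the cut-offs, and then also supplies the accuracy by which they are judged. A fitted model follows chance features of its own sample, and a cut-off picked from that sample follows them further. Accuracy computed in the same patients is therefore higher on average than the strategy will achieve in new patients.

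The error falls mainly on sensitivity, which sets the split between detected and missed cases. Missed cases would be understated for the strategy that is recommended. Strategies may also be affected unequally: the echocardiography-only strategy does not pass through the p-value selection, so its comparison with the fitted strategies may be tilted.

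**Working it through.** **1. The plan's own figures reproduce.** Determinants × events per determinant = 9 × 10 = 90 events. 90 / 0.15 = 600 participants. 600 / 0.50 = 1200 invited, matching "a response rate of at least 50%, approximately 1200 patients will be invited".

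**2. Patients available for modelling.** The Study population section expects 30 of the 600 responders to have known heart failure, and these receive questionnaires only. If they count within the 600, 600 − 30 = 570 are assessed. Expected cases are 570 × 0.15 = 85.5, and events per determinant are 85.5 / 9 = 9.5. The range is therefore 570 to 600 patients and about 85 to 90 cases.

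**3. Simulation.** The article gives no effect sizes and no rule for choosing cut-offs, so the following are assumptions:

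- independent normal predictors and 15% prevalence;
- nine candidates of which four or five carry signal, or three informative ones (standing for score, NT-proBNP and ECG);
- true AUC about 0.69 to 0.84 for the 600-patient rows; log odds ratios 0.8, 0.5, 0.3, 0.2, 0.1 and four zeros for the nine-candidate 570-patient rows;
- cut-off either at the maximum of sensitivity + specificity (Youden) or at a fixed predicted risk of 15%.

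Each data set is screened at univariable p < 0.15 unless noted. The multivariable logistic model is fitted, and model and cut-off are then applied to a large sample of new patients. Optimism = apparent value − value in new patients.

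| Patients | Candidates | Cut-off | Sensitivity, apparent / new | Optimism (points) | AUC, apparent / new |
|---|---|---|---|---|---|
| 600 | 9, weak effects | Youden | 0.668 / 0.594 | 7.4 | 0.704 / 0.677 |
| 600 | 9, moderate | Youden | 0.738 / 0.671 | 6.7 | 0.787 / 0.767 |
| 600 | 9, strong | Youden | 0.795 / 0.738 | 5.7 | 0.848 / 0.833 |
| 600 | 3, weak | Youden | 0.670 / 0.621 | 4.9 | 0.689 / 0.686 |
| 600 | 3, moderate | Youden | 0.735 / 0.685 | 5.0 | 0.779 / 0.769 |
| 600 | 3, strong | Youden | 0.785 / 0.745 | 4.0 | 0.839 / 0.835 |
| 570 | 9 | Youden | 0.717 / 0.642 | 7.5 | not tabulated |
| 570 | 9, no screen | Youden | 0.730 / 0.659 | 7.1 | not tabulated |
| 570 | 9 | fixed 15% | 0.692 / 0.657 | 3.5 | not tabulated |
| 570 | 3 | fixed 15% | 0.681 / 0.669 | 1.2 | 0.750 / 0.742 |

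The calibration slope in new patients was 0.85 to 0.93 with nine candidates and 0.92 to 0.97 with three (600-patient rows).

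**4. In counts.** Take the nine-candidate, moderate row with 90 cases. True positives are 90 × 0.738 = 66.4 apparent and 90 × 0.671 = 60.4 in new patients. False negatives are 23.6 and 29.6, so about 6 missed cases go uncounted. Specificity in that row is 0.722 / 0.713. Among 510 non-cases, 510 × 0.009 = 4.6 false positives go uncounted. At the favourable end, 85.5 × 0.012 = 1.0 case.

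**5. Where the optimism comes from.** At 570 patients and nine candidates, moving from the Youden cut-off to the fixed threshold cuts the sensitivity optimism from about 7.5 to 3.5 points. Going from nine candidates to three at the fixed threshold cuts it to 1.2. Removing the p < 0.15 screen does little: 7.5 becomes 7.1 in one set of runs, and in a second set 6.9 (0.715 / 0.646) becomes 7.6 (0.724 / 0.648). In that second set the AUC gap goes from 0.024 (0.757 / 0.733) to 0.029 (0.762 / 0.733).

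**The case against.** The article condenses a fuller protocol, and internal validation is often described elsewhere. That is fair, so the absence of a bootstrap is not in itself the point. The point is that the article fixes same-data selection of tests, cut-offs and strategies and names the best strategy from those patients. The model it calls validated is the Markov cost model, not the diagnostic one, and varying prior assumptions is not an optimism correction.

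The search is also restrained. Clinical findings enter as one score with a cited source, the order follows clinical practice, and the study is planned at 10 events per determinant. This stands, and it is why the low end of the range is only about 1 point.

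A reader might infer several stronger things that the document does not support:

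- **That the p < 0.15 screen is the culprit.** Removing it gives no consistent reduction in optimism. That it may drop a test useful only jointly with others is possible but unquantified.
- **That one figure, such as six points of sensitivity, describes this study.** The Youden rule is an assumption. The article names no criterion and ranks strategies by cost-effectiveness. Nor does it describe backward elimination; p < 0.10 serves to judge added value.
- **That the ranking will favour the most heavily tuned multi-test strategies.** No ranking was simulated. The article itself expects echocardiography to weigh heavily in the panel diagnosis, which would raise the apparent accuracy of the echocardiography-only strategy for a different reason. The net tilt is therefore unknown.
- **That NT-proBNP will be dichotomised in the model.** The article does not say so.

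**Conclusion.** The concern holds in this form: strategies and cut-offs are selected and evaluated in the same patients, and nothing in the article corrects for it. The direction is secure, since apparent accuracy was too high in every scenario. The size depends on assumed effects and an assumed cut-off rule. It runs from about 1 to about 7.5 points of sensitivity (roughly 1 to 6 of 85 to 90 cases) and from less than 0.01 to about 0.03 in AUC. Model fitting and data-chosen cut-offs account for most of it. Whether the cost-effectiveness ranking would change is open. This should be changed because it bears on a primary objective and is cheap to correct, but it does not invalidate the design.

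**What to change.** 1. Bootstrap the entire stated procedure: determinant selection, test combinations, cut-off choice and choice of strategy, repeated in each resample. Alternatively, prespecify the cut-offs and bootstrap the rest, because fixed cut-offs remove only part of the optimism.
2. Report optimism-corrected AUC, sensitivity and specificity beside the apparent values.
3. Use the corrected true-positive, false-positive, true-negative and false-negative counts, with their uncertainty, in the cost-effectiveness analysis. Report how often the chosen strategy ranks first across resamples, which would answer the open question about the ranking.
4. Secondary: drop the p < 0.15 screen and enter the determinants in the stated chronological order, since the sample was sized to fit all nine together. This simplifies the model but does not remove the optimism, so it does not replace steps 1 to 3.

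The cost is analysis wording, some programming and slightly lower reported accuracy. No new data or patients are needed.

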### Secondary objectives

- To assess the impact of heart failure, and the combination of new diagnosis of HF with accordingly treatment in patients with diabetes type 2 on health status.

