### Health status measurement

To assess the impact of (detecting and treating previously unknown) heart failure on the health status the participants will receive a questionnaire (including questions on health status) to be completed during their visit to the diagnostic centre at baseline. The group known with a cardiologist-confirmed diagnosis of heart failure will be visited at home. After 3 months and after 12 months from baseline measurement the participants will receive the same questionnaires, including an additional questionnaire with questions about possible change in medication.

In order to calculate quality-adjusted life years (QALYs) preference-based utilities will be measured with the EuroQol-5D instrument [26]. Generic health status will be assessed with the Short Form 36 (SF36) [27-29]. For disease specific health status the diabetes health profile (DHP) will be used [30]. These questionnaires are all widely tested and used.

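### Secondary health-status objective: 18 to 54 separate t-tests and ANOVAs, partly redundant and with no lead score or contrast named, where one repeated-measures model would serve better (minor)

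*Protocol article*

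**What the plan says.** The protocol article lists the aim under Secondary objectives, with health status as the outcome: "To assess the impact of heart failure, and the combination of new diagnosis of HF with accordingly treatment in patients with diabetes type 2 on" that outcome. It holds two questions: the impact of heart failure, and the impact of a new diagnosis with treatment.

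The Health status measurement section names three instruments. EQ-5D supplies utilities for QALYs. For the SF-36 it says "Generic health status will be assessed with the Short Form 36 (SF36"). For the third, "For disease specific health status the diabetes health profile (DHP) will be used". Table 1 schedules all three at baseline, 3 months and 12 months.

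The Statistical analysis section defines "three groups (no heart failure, known heart failure and previously unknown heart failure"), whose scores "will be compared at baseline (t0) and on 3 months and 12 months. Also the difference between 0-3 months, 3-12 months and 0-12 months". These changes are taken for each patient, and the text goes on to say that they "will be compared between the groups (T-test and ANOVA").

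No score, time point, change or pair of groups is put first. No significance level or multiplicity rule is given for these tests. The only p-value thresholds in that section, 0.15 and 0.10, belong to the diagnostic model.

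**The concern.** The article does more than leave this analysis open: it chooses a grid of separate tests, and the grid has three weaknesses.

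- It is not mapped to the two questions in the objective. A reader of the results cannot tell which comparison was meant to answer which question, and any one of many could be put forward as the impact of heart failure.
- It is partly redundant. Testing all three changes besides all three levels adds tests without adding information.
- It handles each time point alone. The Abstract makes follow-up a matter of the patient's permission, so the 0, 3 and 12 month comparisons may rest on different patients. A change score drops anyone missing either measurement. This matters most in the known heart failure group, expected to number at most about 30.

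At stake is how a nominally significant health-status difference can be read. The prevalence and diagnostic results are not affected.

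**Working it through.** **The plan's own figure.** The Power calculation section gives 9 determinants × 10 events = 90 cases; 90 / 0.15 = 600 participants; 600 / 0.50 = 1200 invited. These figures reproduce. They size the diagnostic model, and no sample size is stated for the health-status comparisons.

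**Inputs from the article.** Three instruments; three groups, so three pairs; three time points; three changes. Expected group sizes: known heart failure 30 (Study population, an upper bound), previously unknown 90, and by subtraction 600 − 30 − 90 = 480 without heart failure.

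**Count.** Analyses per score: 3 levels + 3 changes = 6.
- ANOVA only: 3 instruments × 6 = 18.
- Every pair t-tested, one score per instrument: 3 × 6 × 3 = 54, of which 27 are on changes.

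**Redundancy.** With Y0, Y3 and Y12 the scores at the three times, (Y3 − Y0) + (Y12 − Y3) = Y12 − Y0. All six quantities are linear functions of three measurements.

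**Chance of at least one false positive.** Assumptions not in the article: two-sided 0.05 per test, no true difference anywhere, one score per instrument, correlation between times 0.5-0.85, correlation between instruments 0.3-0.9, no missing data. The independent case is 1 − 0.95^k for k tests. The simulation used groups of 480/30/90 and 6000 runs per setting.

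| Set of tests | k | Independent | Simulated |
|---|---|---|---|
| All pairs, t-tests | 54 | 0.937 | 0.55-0.78 |
| ANOVAs | 18 | 0.603 | 0.31-0.49 |
| t-tests only after a significant ANOVA | up to 54 | - | 0.31-0.49 |
| Previously unknown versus no heart failure only, t-tests | 18 | 0.603 | 0.30-0.48 |
| One instrument, all pairs, t-tests | 18 | 0.603 | 0.39-0.43 |
| One instrument, ANOVAs | 6 | 0.265 | 0.19-0.22 |

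The expected number of false positives is 54 × 0.05 = 2.7, or 18 × 0.05 = 0.9 with ANOVAs only. The simulated chances lie below the independent ones because the tests overlap; the linear dependence is part of that overlap.

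**After the fix.** One score and one contrast: 0.05. Two lead contrasts, one per question, each at 0.05: at most 2 × 0.05 = 0.10 for either. Cutting down to one instrument while keeping all six analyses is not enough, as the last two rows show.

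**The case against.** The strongest reply is that this is a secondary objective, aimed at assessing an impact, with no hypothesis, significance level or success rule attached. The article condenses a fuller plan, and a hierarchy or correction may stand in an analysis plan that is not shown. That stands: one can say only that no correction is stated here, not that the analysis is uncorrected. It is also the main reason the point is minor. It does not cover the part that the article does fix, namely separate tests on six overlapping quantities per score.

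Several stronger readings are tempting, and the documents do not support them.

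- A reader might infer that at least 54 tests are planned. The text says "will be compared between the groups (T-test and ANOVA"), without saying that every pair is t-tested. On one score per instrument the floor is 18 ANOVAs.
- A reader might infer that a false positive is nearly certain, for instance by adding subscales. The article does not say which scores or subscales will be analysed; Table 1 gives item counts only.
- A reader might infer that the linear dependence of the changes inflates the error. It is redundancy, and overlap lowers the family-wise error compared with independent tests.
- A reader might infer that all 54 tests bear on the impact of heart failure. A third of them, 18, compare two heart failure groups.
- A reader might infer that the diabetes questionnaire counts equally with the others. The article gives the three instruments different roles.

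It is also fair to say that the all-null case is least informative at baseline. The reference standard requires indicative symptoms for systolic and isolated diastolic heart failure, so some baseline difference in health status is to be expected. And per-time comparisons are not invalid in themselves; they are less efficient and harder to interpret together.

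**Conclusion.** The point holds as a minor one. The stated analysis is a grid of 18 to 54 separate tests with no lead score or contrast named, and its six analyses per score contain only three linearly independent quantities. If nothing truly differed, at least one p<0.05 would turn up with a chance of about 0.31-0.49 (ANOVAs) to 0.55-0.78 (all pairs by t-test). A false positive is therefore more likely than not only on the pairwise reading.

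These figures rest on the assumed 0.05 level, correlations, complete data and one score per instrument. The preference for a joint model does not depend on them: it follows from three repeated measurements, follow-up by permission, and a small known heart failure group.

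**What to change.** - Replace the separate tests with one repeated-measures mixed model per score, with group, time and group × time, using all available measurements. Patients with partial follow-up then stay in, on the assumption that missingness depends only on observed data.
- Name one lead score. A generic one suits the objective, because the Diabetes Health Profile concerns a condition that all three groups share.
- Name one lead contrast for each half of the objective: heart failure versus no heart failure in level (with the time point stated) for the impact of heart failure, and the 0-12 month change in previously unknown heart failure versus no heart failure for new diagnosis with treatment.
- Report all other contrasts from the same model as exploratory estimates with confidence intervals, and drop the redundant separate test of the 3-12 month change.

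The cost is a change of analysis wording only; data collection is unchanged. The downside is that the other scores and contrasts can no longer be presented as confirmatory. If the full analysis plan already contains such an ordering, a sentence pointing to it would be enough for the multiplicity part.

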## Background

Cardiovascular diseases account for up to 80% of the excess mortality in patients with diabetes type 2 (DM2) [1]. Processes underlying this excess cardiovascular risk include coronary atherosclerosis, microvascular disease and autonomic neuropathy [1]. Importantly, morphological myocardial abnormalities and eventually diabetic cardiomyopathy and heart failure (HF), i.e. left ventricular dysfunction with symptoms of heart failure play a role [2,3]. Notwithstanding the high rate of cardiovascular diseases and the availability of morbidity and mortality reducing treatment for heart failure, [4] up to now, only a few studies assessed the prevalence of HF in diabetic patients. These studies showed a prevalence of HF of 12-22% in the subgroup of diabetic patients who had been admitted to the hospital [5,6]. In another study, the incidence rate of HF in DM2 patients was about 2.5 times higher than in non-diabetic control subjects [7]. Importantly, the diagnosis of HF in the aforementioned studies was based on hospital discharge diagnoses. To our knowledge, there are no studies that assessed HF using a diagnostic strategy including echocardiography in a representative sample of patients with diabetes in primary care (not selectively in those admitted to a hospital) [8,9]. Hence, valid prevalence estimates of HF in patients with diabetes type 2 are lacking. Such studies are needed because the majority of patients with diabetes is managed in primary care [10]. The diagnosis of HF however is notoriously difficult in the early phases of the syndrome and in the presence of co morbidities, such as chronic obstructive pulmonary disease (COPD) and obesity [11]. Moreover, echocardiography, the cornerstone investigation to diagnose HF, [4] is usually not ready at hand for primary care patients. Studies indicate that 50% of all patients (thus not only those with DM2) with HF in primary care remain undetected [10]. Recently, our group showed that unrecognised HF was common (prevalence 20.5%) among primary care patients with COPD aged ≥ 65 years [12]. High prevalence of unrecognised HF can therefore also be expected in patients with diabetes in primary care.

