## Methods/design

### Study design

A prospective diagnostic efficiency study. See figure 1 for the study scheme and table 1 for the measurement scheme.

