### Reference standard of heart failure

Presence or absence of HF will be determined by an outcome panel consisting of two cardiologists and one GP. In analogy with earlier studies, the panel will use all available information from the diagnostic work-up, including echocardiography, but except the NT-proBNP results (to prevent incorporation bias pertaining to this particular test). Consensus diagnosis by an outcome panel is an established method in case an irreproachable reference standard is lacking, as is the case for HF [8,9]. Outcome panels have been successfully applied in earlier studies of HF by our group and the reproducibility of this method is high [13]. In case of no consensus the majority decision will be used. Patients classified as HF by the panel will be further classified as systolic or 'isolated' diastolic heart failure or 'isolated' right sided heart failure. For systolic heart failure, patients have to have an echocardiographic left ventricular ejection fraction ≤ 45% in combination with presence of symptoms indicative of heart failure (that is, orthopnoea, paroxysmal nocturnal dyspnoea, fatigue, peripheral oedema, nocturia more than twice a night, or any combination of these symptoms). For isolated diastolic ventricular dysfunction, patients have to have echocardiographic diastolic dysfunction and a left ventricular ejection fraction > 45%. For isolated diastolic heart failure patients have to have echocardiographic diastolic abnormalities in combination with indicative symptoms and signs (that is, peripheral or pulmonary fluid retention or raised jugular venous pressure) of heart failure [24] or indicative symptoms and echocardiographic left ventricular hypertrophy, atrial fibrillation, or anginal complaints [25].

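### The health-status objective asks for the impact of heart failure and of its detection and treatment, but the named t-tests and ANOVA on three groups formed by HF status can show only association

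*Protocol article*

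**What the plan says.** The Secondary objectives section of the protocol article sets the aim: "To assess the impact of heart failure, and the combination of new diagnosis of HF with accordingly treatment in patients with diabetes type 2", with health status as the outcome. The Health status measurement section repeats it as the reason for the questionnaires: "To assess the impact of (detecting and treating previously unknown) heart failure on the health status". Both wordings ask about an effect of HF and an effect of finding and treating it.

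The design is described as "A prospective diagnostic efficiency study". Nothing is allocated. Under Statistical analysis, the questionnaire scores of "the three groups (no heart failure, known heart failure and previously unknown heart failure) will be compared at baseline (t0") and again at 3 and 12 months. The next sentence adds the change scores: "Also the difference between 0-3 months, 3-12 months and 0-12 months within patients, will be compared between the groups (T-test and ANOVA"). These are the only methods named for this objective. The same section specifies multivariable logistic regression for the diagnostic question.

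Table 1 lists demographic parameters and medical history at baseline. The Diagnostic assessment section adds time since diabetes diagnosis, taken from the GP files. For patients with known HF, the Study population section provides for questionnaires and a file search for comorbidities and date of HF diagnosis.

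**The concern.** The aim and the method do not match, in two separate ways.

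- **Confounding.** Patients enter a group because they do or do not have HF. People with HF may differ from the others in age, sex and comorbidity, which also bear on health status. The Background itself notes that HF is hard to diagnose "in the presence of co morbidities, such as chronic obstructive pulmonary disease (COPD) and obesity". A plain comparison of means attributes all such differences to HF.
- **No comparator for detection and treatment.** All newly detected patients are in one group. Neither patients without HF nor patients whose HF was already known show how the newly detected would have fared had they stayed undetected.

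If the plan is followed as written, the secondary objective would be answered by a group difference that may be partly confounded, and by a change over time that cannot be attributed to treatment.

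**Working it through.** **1. The plan's own figures.** The Power calculation section gives 9 determinants and 10 events each: 9 × 10 = 90 patients with unknown HF. At 15% prevalence, 90 / 0.15 = 600 participants; at 50% response, 600 / 0.50 = 1200 invited. Study population expects 0.05 × 600 = 30 with known HF. All of this reproduces. The size was set for the diagnostic model; the article states no effect size or power for health status. The implied groups are about 90 unknown HF, 30 known HF and 600 − 90 − 30 = 480 without HF.

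**2. What each comparison removes.**

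| Comparison | Stable additive differences (age, sex, comorbidity) | Different trajectories by age or comorbidity | Regression to the mean | Effect of diagnosis plus treatment |
|---|---|---|---|---|
| Scores at 0, 3, 12 months | remain | remain | not applicable at baseline | not identified |
| Within-patient change | cancel | remain | some remains | not identified |

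Regression to the mean enters because group membership depends partly on baseline symptoms. For systolic HF these include "orthopnoea, paroxysmal nocturnal dyspnoea, fatigue, peripheral oedema, nocturia more than twice a night", some of which plausibly lower a health-status score on the same day.

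**3. Illustration for one time point (inputs assumed, not in the documents).** Let d be the standardised imbalance of a confounder between two groups and r its correlation with the score. The bias of the unadjusted mean difference is d × r, in SD of the score.

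- With d = 0.3 to 0.8 and r = 0.2 to 0.4, the bias is 0.3 × 0.2 = 0.06 to 0.8 × 0.4 = 0.32 SD.
- For unknown versus no HF, SE = √(1/90 + 1/480) = 0.115 SD, so the 95% half-width is 1.96 × 0.115 = 0.23 SD.
- If HF has no effect, the two-sided 5% test rejects with probability Φ(b/SE − 1.96) + Φ(−b/SE − 1.96). This is 8% at b = 0.06 and 80% at b = 0.32.
- For known versus no HF (30 against 480) the same biases give 6% to 40%.

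**4. Illustration for change (inputs assumed).** If a share f of a baseline deficit D is transient, the group gains D × f without any treatment. D = 0.3 to 0.8 SD and f = 0.1 to 0.3 give 0.03 to 0.24 SD. If none of the deficit is transient, the gain is zero. The documents give neither D nor f.

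**5. One further difference.** According to Health status measurement, patients with known HF complete the baseline questionnaire at a home visit and the others at the diagnostic visit. Group and setting are therefore mixed at baseline.

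**The case against.** Several points on the other side are sound.

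- The t-test and ANOVA are attached to the sentence on within-patient change, where stable additive differences cancel. A reader might infer that age and comorbidity invalidate the change comparison outright. They do not: that confounding bears on the comparisons at each time point, and only differing trajectories carry over into change.
- For the comparisons at each time point the article says only that groups are compared. That they are unadjusted is partly inferred, and an article may leave covariates to a fuller document. This softens the first defect. It does not touch the second, since no analysis plan can supply a comparator that the design lacks.
- A reader might size regression to the mean as if patients had been selected on the questionnaire score. They are not. A panel classifies them from the full work-up, with an echocardiographic finding required for systolic and isolated diastolic HF, and a lasting deficit from structural disease does not regress. Some regression is plausible; its amount is unknown.
- The article states no rule that the change in the newly detected group will be read as a treatment effect, and there is a concurrent group without HF. That is correct; the difficulty is the wording of the objective that this comparison is meant to answer.
- A reader might add that HF patients will drop out more, that every pair of groups is tested each time, or that three change intervals are redundant. The article gives no dropout figures and does not say that all pairs are tested (one ANOVA for each of three time points and three intervals gives six tests per scale). Showing early, later and total change is a legitimate choice.
- The objective is secondary.

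**Conclusion.** The mismatch is real and should be put right, at the level of a secondary objective. Two conclusions need no assumed number: the group comparisons at 0, 3 and 12 months are open to confounding with the methods named, and the effect of diagnosis plus treatment is not identifiable from these three groups under any analysis.

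The size of the bias cannot be derived from the documents, which give no age gap, comorbidity difference, retest correlation or dropout by group. The range of 0.06 to 0.32 SD rests on assumed imbalances and correlations. It shows only that a bias comparable to the sampling error (0.23 SD) is possible; with no imbalance there is none. A firm statement that the result is biased by so many points would go beyond the evidence.

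**What to change.** **Analysis.** Replace the t-tests and ANOVA by one linear mixed model per scale, using all available scores at 0, 3 and 12 months, with group, time and group-by-time. Name the 0-12 month change as the main contrast. Adjust for covariates available in all three groups: age, sex, diabetes duration, and comorbidities from the medical files such as ischaemic heart disease and COPD. Confirm that diabetes duration is also extracted for patients with known HF. Use BMI only if it is recorded in all groups; the article does not list it. Covariate main effects adjust the level of the scores. To adjust the change contrast for differing trajectories, add covariate-by-time terms.

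**Wording.** State the objective, in Secondary objectives, Health status measurement and the abstract, as the association of HF with health status and the course of health status after detection, without a claim about the effect of diagnosis and treatment. This is needed in any case, because the model does not supply the missing comparator or remove regression to the mean.

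**Cost.** Analysis-plan wording and a check of covariate availability; no new patients or visits. The downside is a more modest secondary claim.
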